### Design

1.1

This exploratory study uses an observational n-of-1 design [36], involving repeated measurements of self-reported, behavioural, and physiological outcomes over the time of one year (365 days) within individuals without manipulation of variables by the investigators. The work is carried out in accordance with the World Medical Association Declaration of Helsinki [37]. Ethical approval has been granted by the Ethics Committee of the Department of Medicine at Goethe University Frankfurt, Germany (date: 24/08/2023, reference number: 2023–1309). The study protocol has been registered in the German Clinical Trials Register (reference number: DRKS00032618).

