### Study population

1.2

We aim to collect 10–12 complete case studies of adult patients with depressive disorders; allowing for some dropout, *N* = 15 participants will be included. Patients are recruited at the Department of Psychiatry, Psychosomatic Medicine and Psychotherapy, University Hospital of Goethe University Frankfurt, Germany. This study protocol is presented to treating physicians and psychologists at various occasions and a flyer with the inclusion and exclusion criteria (see Table 1) is provided. Physicians and psychologists invite patients who are receiving treatment for affective disorders to participate in the current study. Interested patients provide their contact details and written consent to be contacted by the study centre. If sufficient participants can't be reached, various communication channels of the German Foundation for Depression and Suicide Prevention (e.g., newsletter, website, online discussion forum) shall be used to draw the attention of interested participants to the study.

**Table 1 tbl1:** Inclusion and exclusion criteria for study participation.

Inclusion criteria	Exclusion criteria
- Minimum 18 years old	- Acute risk of self-hazard/suicidality (six months before inclusion)
- Diagnosis of a recurrent major depression (ICD-10 F33) with two or more depressive episodes during the last ten years	- Currently severe depressive episode with psychotic symptoms (F33.3)
- Currently residual symptoms of depression (BDI-2 sum score ≥14)	- Lifetime diagnosis of any psychotic disorder (any diagnosis according to ICD-10 F2)
- Being in concurrent treatment for the depressive illness	- Lifetime diagnosis of any bipolar disorder (ICD-10 F31)
- Being able to provide informed consent	- Lifetime diagnosis of any borderline personality disorder
- Usage of an own Android smartphone (or agreement to switch to an Android smartphone provided by the study centre)	- Severe somatic illnesses requiring intensive treatment
- In case of any lifetime substance abuse disorder: being in stable remission (min. 6 months)	

Note: ICD-10 = International Classification of Diseases, Tenth Revision, BDI-2 = Beck Depression Inventory-II.

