To address RQII, i.e. “Can personal MS data predict the self-reported depressive symptom severity on a) the next day(s) and/or b) the next week(s)?“, we apply various machine learning techniques. Exploratory analyses investigate the predictability of depressive symptoms within individuals, using either classification or regression approaches. We compare idiographic models, which use data from individual patients, with nomothetic models based on data from all participants. Furthermore, we plan to examine whether multitask-learning methods [57] can enhance performance. Modern machine learning models, such as deep neural networks (DNNs), are validated against classical state-of-the-art methods, including boosted ensemble techniques [58], support vector machines [59], and autoregressive models [32] focusing on vector autoregressive (VAR) models and their analyses using forecast error variance decomposition (FEVD) and impulse response functions (IRF) specifically for idiographic approaches. Individual thresholds for high depressive symptom severity are derived from the data. Using eXplainable AI (XAI) methods, we evaluate the sensor technology component within iTD to understand the significance and impact of various MS features on the model's outcomes. This will help to identify the most relevant aspects of the MS data and clarify their influence on potential decision-making processes. Models based on data from all participants are validated using leave-one-subject-out cross-validation (LOSO-CV) [60,61], while within-subject models employ time-series cross-validation [62,63] and rolling back cross-validation [64].

For both RQ, sensitivity analyses will be conducted using different amounts of input data (e.g., 12 vs. 24 h of MS data, all AA vs. only MS data).

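### Idiographic and nomothetic models are to be compared, but under validation schemes that answer different questions, so a performance difference cannot be read as the value of personalisation

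*Protocol article*

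**What the plan says.** Section 1.6 (Data analysis) of the protocol article plans the contrast directly: "We compare idiographic models, which use data from individual patients, with nomothetic models based on data from all participants". Later in the same paragraph it assigns the validation: "Models based on data from all participants are validated using leave-one-subject-out cross-validation (LOSO-CV) [60,61], while within-subject models employ time-series cross-validation" and, in addition, rolling-back cross-validation.

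The outcome form is left open, "using either classification or regression approaches", with person-specific thresholds for high severity. Sensitivity analyses vary the inputs, including all ambulatory data (which contain self-report) against sensor data only. Multitask learning is a further option: "we plan to examine whether multitask-learning methods [57] can enhance performance". Section 1.6 also declares the study exploratory. It names no common test set for the contrast, and no scheme in which the nomothetic model may learn from the test patient's earlier data.

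**The concern.** The two schemes estimate different quantities. Under leave-one-subject-out, nothing from the test patient enters training; the model learns from the other patients' full years. Under within-patient time-series validation, the model has been trained on that patient's own past, including the usual symptom level, but on far fewer observations, especially in early folds. Between the two scores, three things change at once: whether relations are personal or common, whether the patient's level was available for training, and how much training data there was.

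The contrast matters to the paper's argument. The introduction cites a study in adolescents where personalised models did better than universal ones and says this has not been replicated in adults. If personal models score better here, readers will take that as replication. The gain could come entirely from knowing the person's mean, which needs no personalised sensor model.

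**Working it through.** **Inputs from the protocol.** Section 1.2: "We aim to collect 10–12 complete case studies of adult patients with depressive disorders; allowing for some dropout, *N* = 15 participants will be included". Section 1.1: "over the time of one year (365 days) within individuals", so at most about 365 daily PHQ-2 and about 52 weekly PHQ-9 values per patient. There is no stated performance figure to reproduce.

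**Assumptions (none from the protocol).** Identical slopes in all patients, so personalised relations add nothing; linear ridge models; within-person outcome SD 1; within-person R² 0.20; 12 patients; 10 features; no residual autocorrelation; 40 simulated studies per setting. The between-patient SD of the level is τ, and ICC = τ²/(1+τ²): τ = 0.25, 0.5, 1 give 0.06, 0.20, 0.50. The matched column uses common slopes with the patient's own past mean, on the same later days as the idiographic model.

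| Series | τ (ICC) | Idiographic RMSE | LOSO RMSE | LOSO relative to idiographic | Runs where idiographic looks better | Matched common-slope RMSE |
|---|---|---|---|---|---|---|
| Daily | 0 (0) | 0.930 | 0.896 | −4% | 0% | 0.899 |
| Daily | 0.25 (0.06) | 0.932 | 0.943 | +1% | 68% | 0.901 |
| Daily | 0.5 (0.20) | 0.933 | 1.043 | +12% | 98% | 0.901 |
| Daily | 1 (0.50) | 0.930 | 1.362 | +46% | 100% | 0.899 |
| Weekly | 0 (0) | 1.167 | 0.905 | −22% | 0% | 0.925 |
| Weekly | 0.25 (0.06) | 1.172 | 0.936 | −20% | 0% | 0.924 |
| Weekly | 0.5 (0.20) | 1.160 | 1.038 | −11% | 2% | 0.923 |
| Weekly | 1 (0.50) | 1.171 | 1.408 | +20% | 95% | 0.930 |

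In the matched comparison the idiographic model never won, in any completed setting.

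**Why.** With slopes well estimated but the new patient's level unknown, LOSO mean squared error is about (1−R²) + τ²(1 + 1/(N−1)). For N = 12 and τ = 1: 0.8 + 12/11 = 1.891, RMSE 1.375 (simulated 1.362). For ICC 0.3, τ² = 0.3/0.7 = 0.429: 0.8 + 0.429 × 12/11 = 1.268, RMSE 1.126, which is 1.126/0.930 = 1.21 times the idiographic value. The idiographic model pays no τ² but pays for estimating its slopes from one patient's past.

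**Break-even.** Setting τ² × 12/11 equal to the difference in squared error at τ = 0:
- Daily, 10 features: (0.930² − 0.896²) × 11/12 = 0.057, ICC about 0.05.
- Daily, 20 features: (0.967² − 0.896²) × 11/12 = 0.121, ICC about 0.11.
- Weekly, 10 features: (1.167² − 0.905²) × 11/12 = 0.498, ICC about 0.33.
- Weekly, 20 features: (1.360² − 0.915²) × 11/12 = 0.928, ICC about 0.48.

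Above the break-even the idiographic model looks better although slopes are common; below it LOSO does.

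**Other settings.** With 5–10 features and early or mid-year starts, daily LOSO was 19–22% worse at ICC 0.3 and 41–45% worse at 0.5; weekly it ranged from 2% better to 13% worse at 0.3, and was 16–34% worse at 0.5. With R² 10%, five features and a mid-year start, the daily figures were 19% and 43%, the weekly ones 9% and 29%.

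**Level-free metrics** (12 patients, 10 features). LOSO was ahead in every run at every τ. Daily: within-person correlation about 0.44 against 0.38, AUC at a person-specific median threshold about 0.70 against 0.68. Weekly: about 0.42 against 0.19, and 0.69 against 0.59.

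**Same days alone.** A plain pooled model scored on the same later blocks, with the patient's past in training but no person-level term, stayed close to LOSO: 1.030 against 1.043 at τ = 0.5, 1.327 against 1.362 at τ = 1. The person-level term is what closes the gap.

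**The case against.** A reader might infer that the schemes fix the answer in favour of idiographic models even when a common model is true. The documents do not support that. If levels are common too, LOSO wins. It also wins in most weekly settings with small level differences, and on the level-free metrics that classification at individual thresholds suggests.

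Nor does the protocol say that a LOSO model is blind to the patient's level. LOSO removes the patient from training, not from the inputs at prediction, and section 1.6 allows autoregressive models and all ambulatory data as input. In a simulation with the last PHQ value and a short running mean added as inputs (R² 10%, 10 features, ICC 0.3–0.7, mid-year start), the daily gap fell from 20–84% to 1–5%, and weekly LOSO became 14–21% better. This stands: the large daily figures apply to sensor-only models with a level-dependent error.

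It is also tempting to say that the LOSO rule breaks multitask learning, since an unseen patient has no trained task-specific part. The protocol does not say that LOSO is applied to multitask models, so this is inference only.

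Finally, the study is an exploratory pilot, the RQII wording asks only whether individualised models can forecast, and metric and centring are details an article may leave to a fuller plan. That lowers the severity. But the contrast and the two schemes are stated rules, and exploratory status does not make an unmatched contrast interpretable.

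**Conclusion.** The point holds in conditional form. Followed as written, the comparison confounds personalised relations with access to the patient's own level and with the amount of training data.

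- **Towards idiographic models:** patients differ in mean level, the metric depends on level (such as RMSE), and inputs are sensor-only. Daily LOSO error is then about 20% worse at ICC 0.3 and 40–46% worse at 0.5, and the ranking reverses the matched one.
- **Towards nomothetic models:** level differences are small, weekly series are short, or the metric is level-free.

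Slopes were common throughout, so in the second group the ranking agrees with the matched one; how far the schemes could wrongly favour nomothetic models when slopes are personal was not simulated. The sizes rest on linear models, assumed R², feature numbers and between-patient variances, and equal feature means across patients. The mismatch in test days alone matters little. Severity: should be fixed.

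**What to change.** State in section 1.6, or in the analysis plan behind it, wording such as: *For the comparison of idiographic and nomothetic models, and of multitask models if they are compared, all models are scored for each patient on the same forward-chained test days, using only days with an observed PHQ value. Nomothetic models are trained on the other patients plus the target patient's data up to the forecast origin, with a person-level offset or centring on that patient's past mean. A forecast equal to the patient's past mean serves as benchmark.*

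Keep leave-one-subject-out as a separate analysis of performance in a new patient, and do not set its scores directly against idiographic scores.

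The cost is wording and more model refits. No new data are needed, which matters because section 1.3.3 reports last patient out in December 2024. The drawback is that only days after the initial training block enter the comparison, which weighs more for the weekly series.

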## Discussion

2

This study aims to deepen the understanding of markers and predictors of individual disease trajectories in patients with depressive disorders. If changes in depressive symptoms can be predicted ahead of time, individuals could try to counteract depression relapse through timely self-management or treatment. They can gather MS data with little intrusion in their daily lives and based on these, self-management guidance and professional interventions for depression shall be offered in a tailored way and at the precise time when they are needed [65].

There are still some challenges to overcome to deploy MS data for facilitating timely self-management advice. One key challenge is deriving meaningful information from the huge datasets generated by MS. Data-driven methods are increasingly used to analyze complex associations, focusing on nonlinear models that identify patterns and dependencies in the input data. DNNs are capable of automatically learning abstractions in the data that can be entirely novel and have demonstrated superior performance over classical machine learning models across a range of tasks [66]. One notable limitation of DNNs, however, is their reliance on large and diverse datasets to achieve optimal performance. Yet, our study includes data from fewer than 30 patients, which may result in bad generalization [67]. Nonetheless, DNNs can still be used to generate complex features (e.g., activity metrics from raw accelerometer data) where sufficient data is available [68]. Additionally, pretrained models can be fine-tuned using transfer learning to mitigate the limitations of small datasets [69]. Another key concern of DNNs is their reputation as a “black box” approach — i.e., they are said to lack transparency or interpretability of how input data are transformed to model outputs [66]. Interpretability is crucial though in fields in which these algorithms' predictions have serious implications, such as psychiatry and digital mental health applications [70]. Where data relationships are inherently complex and probabilistic, enhancing the understandability of AI models through transparency and interpretability is essential to develop trustworthy systems fit for deployment [71]. XAI allows users and parts of the internal system to be more transparent, providing explanations of their decisions in some level of detail. These explanations are important to ensure algorithmic fairness, identify potential bias/problems in the training data, and to ensure that the algorithms perform as expected. Advancing research on XAI is crucial to successfully use MS data for patients’ daily self-management and treatment.

Regulatory and legal aspects represent yet another challenge for the successful deployment of MS data by patients with depression. The international ISO standard (ISO/TS 82304–2:2021), the GDPR and other EU regulations, such as the MDR (Medical Device Regulation) impact the development of mental health applications in European countries [72]. Academic research and product development are today more intertwined than ever, placing the research of fundamental questions into the framework of early product development of health apps [73]. Ensuring high patient protection significantly increases the costs required for clinical research, which raises the question of additional funding for such applications, especially to meet Europe's high regulatory standards.

Participants in the current, purely observational study are going to benefit from their study participation through the continuous self-monitoring of depressive symptoms. This provides a long-term documentation of changes in depressive symptoms, increasing self-awareness and providing new insights towards the self-management of their condition. Self-monitoring and journaling are tools that have been used traditionally for the treatment of any behavioural or emotional problem. Whilst the act of tracking *physical* symptoms resulted in greater symptom reporting in healthy subjects [74], previous studies reported beneficial effects of symptom tracking for *mental* health, including increased self- and symptom awareness [75,76], which in turn facilitated self-reflection and more proactive coping with symptoms [76,77]. Importantly, asking about suicidal thoughts has been shown to *not* provoke suicidal ideation [78].

### Strengths and limitations

2.1

A major strength of the proposed study protocol is the focus on intraindividual processes and the personalization of the data analysis approach. However, there are also some limitations to address: (1) We hope to achieve a very high data density for the individual participants through continuous data collection over the course of one year and constant monitoring of data completeness and quality by the study centre. Potential missing data might pose limitations on the success of the study though. We require daily and weekly self-reports from patients as an indicator of their depressive symptom severity, which bears a risk of non-compliance or fatigue with the study procedures. If patients were more non-compliant on days with stronger depressive symptoms, the prediction of these days with higher symptom burden might get very difficult as this represented an “out-of-sample” prediction in Machine Learning terms. (2) The performance of prediction models may vary across participants and the focus on the individual furthermore bears a risk of overfitting predictive models. Even when we collect contextual information from participants, the data might not fully represent the daily experiences and context of the person, which makes it possible that patterns are related to the specific context of data collection during the year and might not generalize to the life of individuals after participation in the study. (3) The current work is a pilot study for individualized long-term depression modelling. Given the heterogeneity of depression, the symptoms and patterns observed in the current, small sample may not be representative of the broader population of patients suffering from depressive disorders. This limits the generalizability of our findings, which will need to be validated in larger samples.

### Implications and future directions

2.2

To conclude, our study pursues a novel approach to enable patients in the future to use their existing personal data from smartphones and wearables for their disease management. The MONDY project consortium is committed to working towards high interoperability of the developed system, so that it could potentially be integrated into regular care (e.g. as electronic patient records) without major time lags from research to practice [79]. Using their own personal data for a better understanding of their depressive disorder could be empowering for the many individuals living with depression.

## Data Availability

No data was used for the research described in the article.
